## Abstract

**Background:**

Nonspecific neck pain can cause considerable suffering, possible disability and reductions in quality of life and productivity. The aim of the proposed study is to evaluate the immediate effect of acupuncture on pain, cervical range of motion and electromyographic activity of the upper trapezius muscle in patients with nonspecific neck pain.

**Methods/Design:**

A total of 12 patients with nonspecific neck pain and 12 healthy subjects will be enrolled in a randomized, single-blind crossover study. Each subject will receive two forms of treatment in random order: a single session of traditional acupuncture (acupoints: triple energizer 5, ‘*Wai-guan*’ and large intestine 11, ‘*Qu-chi*’) and sham acupuncture. To eliminate carry-over treatment effects, a one-week wash-out period will be respected between sessions. Surface electromyography will be used to determine motor control in the upper trapezius muscle before and after treatment. The outcome measures in the group with neck pain will be a numerical pain rating scale (range: 0 (no pain) to 10 (maximum pain)), documentation of the pain area on a body chart and cervical range of motion. Comparisons before and after acupuncture treatment will demonstrate whether acupoints affect the activity of the upper trapezius muscle, pain and cervical range of motion.

**Discussion:**

The purpose of this randomized clinical trial is to evaluate the immediate effect of acupuncture on pain, cervical range of motion and electromyographic activity of the upper trapezius muscle in patients with nonspecific neck pain. Data will be published after the study is completed. The study will support the practice of evidence-based physical therapy for individuals with nonspecific neck pain.

**Trial registration:**

This trial was registered with Clinicaltrials.gov (identifier: NCT0984021) on 7 November 2013 (https://clinicaltrials.gov/ct2/show/NCT01984021).

## Background

Individuals with nonspecific neck pain (NS-NP) exhibit mechanical alterations and signs of degeneration of the cervical spine [1], causing pain that can irradiate to the upper limbs [2], increased sensitivity, fatigue and stiffness in the muscles of the neck and shoulder, and headache that irradiates to the neck [3]. Changes in muscle behavior in such patients have been demonstrated in studies involving surface electromyography (sEMG) [4-6]. According to one study, there is strong evidence that the motor control of the upper trapezius muscle is directly affected by cervical pain during isometric activities [5]. The studies cited offer preliminary support for the use of treatment methods for NS-NP that emphasize the reestablishment of function in the muscles of the neck. Massage, scapula mobilization, physical therapy, exercise, manual therapy and acupuncture have been reported to be efficient in reducing neck pain [6-10]. However, there is a lack of consensus on the best form of treatment for such patients.

Although acupuncture is accepted and recommended for the treatment of NS-NP [11-13], the arguments used for the effects encountered and the different forms of therapeutic approach hinder a clear understanding of the physiological mechanisms involved. The main limitations regard the different techniques employed, such as either systemic acupuncture [12,14] or in combination with auricular [11,15] or cranial acupuncture [16], or the direct application of needles in trigger points [14,17]. Different numbers of acupoints and forms of needle application within the same treatment technique [11,12,17], as well as variability in the number of sessions (usually ranging from five to 10) [11,12,17], further hamper the choice of this resource for the treatment of NS-NP. In the case of individuals with NS-NP, the improvement in the clinical condition after the use of acupuncture may be attributed to the inhibition of the excitability of the alpha motor neuron [18,19]. However, a thorough review of the literature revealed no studies addressing the effect of acupuncture on motor control in any of the neck muscles in patients with NS-NP.

Changes in muscle activity are generally characterized by the variation and/or reduction in the firing rate of the motor units [20,21], reflecting changes in the myoelectrical pattern of the muscle that can be measured through sEMG [21,22]. Thus, sEMG has been used to determine whether the stimulus from acupuncture has an effect on the activity of skeletal striated muscle [19,23-26]. Some studies have demonstrated a remote effect from acupuncture in the upper trapezius muscle [19,26]. However, further investigations have not found any clinical benefits relating to this discovery. The description of the relationship between the upper trapezius muscle and the acupoints denominated triple energizer 5 (TE-5; ‘*Wai-guan*’) and large intestine 11 (LI-11; ‘*Qu-chi*’) [26] allow the use of sEMG to clarify whether acupuncture truly has a neurophysiological effect on this muscle, the motor control of which is affected in individuals with NS-NP [5].

In clinical practice, the confirmation that acupoints TE-5 and LI-11 act directly on the upper trapezius muscle in patients with NS-NP could contribute toward: i) the standardization of these acupoints as stimuli for the treatment of changes in the upper trapezius muscle stemming from mechanical injury, myofascial tension with and without the presence of trigger points and systemic diseases, such as fibromyalgia; ii) improving the estimation of the effects of treatment; iii) making the use of acupuncture less complex; iv) stimulating the use of acupuncture alone or in combination with other forms of treatment (physical therapy, exercise, massage or manual therapy) and v) allowing the testing of other noninvasive stimuli, such as low-level laser therapy.

The objectives of this study are:To determine whether stimulation with acupuncture at acupoints TE-5 and LI-11 affects sEMG activity of the upper trapezius muscle in healthy subjects and patients with NS-NP andTo determine whether stimulation with acupuncture at acupoints TE-5 and LI-11 contributes to improvements in pain and cervical range of motion in patients with NS-NP.

The first hypothesis is that stimulation with acupuncture at acupoints TE-5 and LI-11 acts directly on sEMG activity of the upper trapezius muscle in healthy subjects and individuals with NS-NP. The second hypothesis is that stimulation with acupuncture at acupoints TE-5 and LI-11 provides immediate improvements in pain and cervical range of motion in patients with NS-NP.

## Methods/Design

### Overview of research design

A randomized, single-blind, sham-controlled, crossover clinical trial will be carried out. The crossover design will be used to exclude the potential interference of individual differences. Figure 1 displays the flow of the study.

**Figure 1 Fig1:**
[figure not shown]
**Flowchart of the study.**

### Study setting

Potential participants will be recruited from patients sent for the treatment of neck pain at the rehabilitation department of the University Nove de Julho. Undergraduate students from the same university will also be asked to participate in the study as the control group (CG).

### Inclusion criteria

Individuals within an age range of 18 to 40 years will be accepted for both groups to minimize any confounding effects stemming from advanced degenerative alterations in the cervical spine. The following will be the inclusion criteria for the NS-NP group (neck pain group (NPG)): score of 15 or more on the Neck Disability Index (adapted and validated for the Brazilian population), which specifically evaluates neck pain and disability [27]; history of neck pain for a period of more than three months; restricted active or passive neck movement in at least one direction and score range of three to six points on an 11-point (range: 0 to 10) numerical rating scale for perceived pain intensity. The inclusion criteria for the CG will be no self-reported history of neck pain and no positive signs of cervical spine or scapular dysfunction during the physical examination.

### Exclusion criteria

The following will be the exclusion criteria for both groups: history of neurological disorders (irradiated pain) or neck surgery; chronic neck pain resulting from a traumatic incident; chronic musculoskeletal condition (such as muscular disorder or polyarthritis); medical diagnosis of fibromyalgia; systemic disease; connective tissue disorder; body mass index <25 kg/m; non-tolerance of needles; current pregnancy; having undergone physical therapy, massage or acupuncture in the previous two weeks or use of analgesic, muscle relaxant, psychotropic agent or anti-inflammatory agent in the previous three days.

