### Outcome measures

The primary outcome of the study is the EMG activity of the upper trapezius muscle after a single session of acupuncture. The secondary outcomes for the study are the numerical rating scale score for pain, pain area and cervical range of motion.

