#### Electromyography

The sEMG signal will be recorded in the dominant upper trapezius muscle in the CG and on the side with the greatest self-reported pain in the NPG. EMG signals will be obtained using an eight-channel module (Model: EMG830C, EMG System do Brazil Ltda™, São José dos Campos, São Paulo, Brasil ), with a band pass filter with cut-off frequencies of 20 to 500 Hz, an amplifier gain of 1,000 and a common rejection mode ratio of less than 120 dB. All data will be acquired and processed using a 16-bit analog-to-digital converter, with a sampling frequency of 2 kHz.

Bipolar surface circular electrodes (Ag/AgCl, Medi-Trace™, Minneapolis, Minessota, United States) with a 10 mm diameter, will be used for the surface recording of EMG, with a center-to-center distance of 20 mm. Before electrode placement, the skin will be cleaned using abrasive paste (EASYCAP™, Woerthsee-Etterschlag, Germany). The electrode will be positioned 2 cm lateral to the midpoint of the line between the C7 spinous process and the acromion [31].

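### As printed, the BMI exclusion admits only people with a BMI of 25 or more; the inequality is unexplained and probably reversed

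*Protocol article*

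**What the plan says.** The Exclusion criteria section opens with "The following will be the exclusion criteria for both groups", and the list that follows includes "body mass index <25 kg/m". The item therefore applies to the neck pain group and to the control group alike.

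The Inclusion criteria section sets a shared age limit ("Individuals within an age range of 18 to 40 years will be accepted for both groups") and adds conditions on neck disability, pain duration, restricted movement and pain score for the patients, and on absence of neck problems for the controls. It says nothing about weight or BMI. No other section restates, explains or qualifies the BMI item.

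Three other statements bear on it:

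- **Source of controls (Study setting):** "Undergraduate students from the same university will also be asked to participate in the study as the control group".
- **Primary outcome (Outcome measures):** "The primary outcome of the study is the EMG activity of the upper trapezius muscle after a single session of acupuncture".
- **Recording method (Electromyography):** bipolar electrodes on the skin "will be used for the surface recording of EMG, with a center-to-center distance of 20 mm".

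**The concern.** An exclusion list names the people who may not enter. With the sign as printed, those people are everyone with a BMI below 25. On the usual classification, in which 25 kg/m² is the lower bound of overweight (an assumption here, since the article does not define it), all normal-weight and underweight people are shut out and every degree of obesity is let in.

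Nothing in the aims asks for that sample, and the measurement argues against it. The eligibility rule decides whom the results describe. If the sign is wrong and the rule was followed, the trial has enrolled a population its authors did not mean to study. If the sign is wrong and the site worked to a different rule, the published criteria do not describe the people enrolled. A reader of the article cannot tell which happened, and the Trial status section says that recruitment is already under way (March to June 2015).

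**Working it through.** The article gives no figure to reproduce. The check is a matter of logic and of comparing sections.

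**Step 1: who remains eligible.** The excluded set is {BMI < 25}, so the eligible set is its complement, {BMI ≥ 25}, subject to age 18 to 40 and the other criteria. The Inclusion criteria contain no BMI condition, so nothing adds an upper limit. The same set results for both groups, that is, for all 12 + 12 = 24 planned participants.

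**Step 2: whether the rest of the article asks for this set.**

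| Section | What it indicates | Fits a sample limited to BMI ≥ 25? |
|---|---|---|
| Background (objectives, hypotheses) | Healthy subjects and patients with nonspecific neck pain, no weight restriction | No |
| Discussion | Results meant to inform physical therapy for people with nonspecific neck pain generally | No |
| Study setting | Controls are undergraduates | No reason given to restrict them this way |
| Inclusion criteria | The age limit is given a reason (to limit confounding by degeneration of the cervical spine) | The BMI item has no reason |
| Exclusion criteria, other items | Diseases, needle intolerance, pregnancy, recent treatment or medication | A BMI below 25 is unlike any of these |
| Outcome measures, Electromyography | Surface EMG of the upper trapezius | Points the other way (Step 3) |

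**Step 3: the direction that the measurement would suggest.** The primary outcome is picked up through the skin and summarised as root mean square amplitude and median frequency. Tissue lying between muscle and electrode weakens and filters that signal. This is general reasoning about the method; the article does not state it. On that reasoning, a BMI limit in this study would be set to exclude high values. The printed sign does the reverse.

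**Step 4: how far apart the two readings are.** Excluding BMI < 25 leaves {BMI ≥ 25}. Excluding BMI > 25 leaves {BMI ≤ 25}. The two eligible sets meet only at BMI = 25, so the choice of sign decides almost entirely who may enter. The number of enrolled people affected cannot be calculated, because the article gives no BMI distribution for either source population.

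**Step 5: effect on the main contrast.** Each participant receives both treatments. EMG-1 and EMG-2 are recorded from the same muscle within one session, at force levels set as percentages of that person's own maximum. Tissue thickness is therefore essentially the same on both sides of each pre/post comparison and of the real/sham comparison. The rule is also identical in the two groups, so it creates no BMI imbalance between them by design. What remains is signal quality and the population to which the results apply.

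**The case against.** The strongest reply is that this is probably a one-character slip in a condensed article. The full protocol and the screening form are not shown, so nobody may have been screened wrongly. That stands as far as actual harm is concerned: the documents do not show that anyone was wrongly enrolled or refused. It does not remove the point. Condensing explains what is left out, whereas this criterion is stated, and stated implausibly. Nor is the sign likely to be a text-reading fault, since the same character appears in its ordinary sense in the significance level under Data analysis.

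A second reply is that the intended direction is inferred. That also stands. The article gives no rationale for any BMI limit, so the reversal is probable and not established, and the authors must confirm it.

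A reader might be tempted to go further in four ways that the documents do not support:

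- **That the unit is wrong as well.** The missing exponent is most likely a superscript lost when the text was read from PDF, and is no finding.
- **That recruitment cannot succeed.** Only 24 people are needed, and the article gives no pool size, screening rate or BMI distribution from which feasibility could be judged.
- **That most volunteers are barred, or that most of those enrolled are protocol violations.** This would need the share of each source population with a BMI below 25, which is not given and may differ between students and rehabilitation patients.
- **That the acupuncture effect would be biased.** The within-person comparison in Step 5 argues against this.

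**Conclusion.** The point holds in limited form. As printed, the criterion restricts both groups to a BMI of 25 or more. That much follows from the text without any assumption. The judgement that the sign is probably reversed rests on three things: the absence of a rationale, objectives that carry no weight restriction, and the general expectation that a BMI limit in a surface-EMG study would exclude high values. The last of these is not in the article.

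The consequence depends on what the site did. If the rule was applied as printed, generalisability is narrower than the stated aims and the EMG signal may be weaker, by an amount the documents do not allow one to quantify; the crossover contrast remains unbiased on this account. If the opposite rule was applied, every participant with a BMI below 25 breaches the published criteria. Either way, a stated eligibility rule that decides who enters both groups needs to be settled before the results can be attached to a population.

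**What to change.** 1. Confirm the intended direction and threshold against the full protocol and the screening form, and state which rule has been applied since recruitment began.
2. If the sign is an error, correct the item in the Exclusion criteria, probably so that it excludes a BMI above 25. If the restriction is intended, give the reason and narrow the target population in the objectives and discussion accordingly.
3. Check everyone already enrolled against the confirmed rule, and report any departures.
4. Report BMI by group with the baseline data.

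The cost is a one-line amendment (or a short justification) and a check of the screening forms for at most 24 enrolled participants. The design, the sample size and the analysis do not change.

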### Randomization and blinding

Each patient will receive two forms of acupuncture in random order: a single session of traditional acupuncture (tACP) and sham acupuncture (sACP). To eliminate carry-over treatment effects, a one-week wash-out period between the treatments will be respected. Randomization in each group will be performed by lots using opaque envelopes containing either the letter A, corresponding to tACP, or B, corresponding to sACP. The participants in each group will be distributed in two subgroups of six individuals based on the initial treatment (tACP and sACP), as shown in Figure 1. When one of the subgroups has completed the treatment course, the order of consecutive arrival of the volunteers will be used until all individuals have been allocated.

Measurements will be performed by five independent researchers. Researcher one will be in charge of the screening process, administration of the questionnaire and randomization of the treatments. Researcher two will be in charge of collecting the EMG data. Researcher three will administer the acupuncture treatment. Researcher four will be in charge of the analysis and processing of the EMG data. Researcher five will be in charge of the statistical analysis of the EMG, pain and cervical range of motion data. The participants will be blinded to the type of treatment and will not be informed that one of the two treatments is a sham procedure. Researchers four and five will also be blinded to both the group allocation and type of treatment.

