### Sample size calculation

The sample size was calculated considering α = 0.05 (5% chance of type one error) and 1-β = 0.99 (% of power of the sample), and data on the amplitude of the EMG signal in the study by Chou *et al*. [26]. The values used were those described by Chou et al. [26] in the period prior to acupuncture (21.3 ± 9.5 μV) and after three minutes of needle manipulation in the acupoints TE-5 and LI-11 (9.5 ± 3.5 μV). The minimum number for each group was determined to be 12 individuals (total = 24).

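### The researcher who screens also draws the lots, so the last treatment-order allocations in each group are predictable to the person deciding eligibility

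*Protocol article*

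**What the plan says.** All of the following comes from the Randomization and blinding section of the protocol article.

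- Method of allocation: "Randomization in each group will be performed by lots using opaque envelopes containing either the letter A" (traditional acupuncture first) or B (sham first). Patients and healthy controls are handled separately.
- Target: each group of 12 is split into two subgroups of six by first treatment.
- Change of rule: "When one of the subgroups has completed the treatment course", then "the order of consecutive arrival of the volunteers will be used until all individuals have been allocated".
- Roles: "Researcher one will be in charge of the screening process, administration of the questionnaire and randomization of the treatments". No separate holder of the envelopes is named.
- Blinding: participants are blinded, and "Researchers four and five will also be blinded to both the group allocation and type of treatment". Researcher one is not on the list of blinded people.
- Design: "Each patient will receive two forms of acupuncture in random order", one week apart.

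The Ethical and data security section places written consent before randomization. Trial status says that recruitment is under way.

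**The concern.** Opaque envelopes conceal an allocation only while its content is uncertain to the person who decides on entry. With a cap of six per order, that uncertainty ends when one order is full. Here the person who has drawn every lot, and can count to six, is also the person who screens.

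Some entry criteria need judgement: restricted neck movement in at least one direction for patients, and absence of signs of dysfunction on physical examination for controls. The timing of entry is also at the screener's discretion. Researcher one could therefore influence, knowingly or not, who receives which order. The last arrivals in a group would also all share one order, which ties order to calendar time.

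What is at stake is the comparability of two sequences of only six people each, and so the protection that random order is meant to give.

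**Working it through.** **The plan's own figure.** The Sample size calculation section gives 12 per group from means 21.3 and 9.5 μV, SDs 9.5 and 3.5 μV, α = 0.05 and power 0.99. The difference is 11.8 and the averaged variance is (9.5² + 3.5²)/2 = 51.25 (SD 7.16).

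- Two independent means, normal approximation, one-sided: 2 × (1.645 + 2.326)² × 51.25 / 11.8² = 11.6, so 12.
- The same, two-sided: 2 × (1.960 + 2.326)² × 51.25 / 11.8² = 13.5, so 14.
- Paired t-test, two-sided, with an assumed pre/post correlation of 0.5: 12 (power 0.994).

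The article states neither the sidedness nor the test. The figure of 12 is reproducible and is not disputed here; it is the number on which the allocation rule acts.

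**When the rule changes.** The trigger is worded as completion of the treatment course. Taken literally, it waits until a subgroup has finished both sessions, and leaves unclear how the limit of six is kept while its last members are in wash-out. The sensible reading is that one order has reached six. Because the subgroups are fixed at six, the people still to come must then all take the other order.

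**How many allocations are forced.** Let k be the number of the 12 still unallocated when one order reaches six. The article does not say how the lots are drawn, so both cases are shown.

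- Independent fair lots (assumption): P(k) = 2 × C(11−k, 5) / 2^(12−k)
- Six A and six B lots without replacement (assumption): P(k) = 2 × C(11−k, 5) / C(12, 6), with C(12, 6) = 924

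| k | Independent lots | 6 + 6 without replacement |
|---|---|---|
| 1 | 504/2048 = 0.246 | 504/924 = 0.545 |
| 2 | 252/1024 = 0.246 | 252/924 = 0.273 |
| 3 | 112/512 = 0.219 | 112/924 = 0.121 |
| 4 | 42/256 = 0.164 | 42/924 = 0.045 |
| 5 | 12/128 = 0.094 | 12/924 = 0.013 |
| 6 | 2/64 = 0.031 | 2/924 = 0.002 |
| Mean | 2.71 (23% of 12) | 1.71 (14% of 12) |
| P(k ≥ 3) | 0.51 | 0.18 |

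At least one and at most six allocations per group are forced. Over both groups the expected number is 2 × 1.71 = 3.4 to 2 × 2.71 = 5.4 of 24.

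**What a steered order can do to the treatment contrast.** Write participant i's traditional-minus-sham difference, leaving carry-over aside, as τᵢ + sᵢπᵢ. Here τᵢ is the treatment effect, πᵢ the change between periods, and sᵢ is +1 for one order and −1 for the other. Averaged over 12 people, the order term is (1/12)Σsᵢπᵢ. If the period change is the same for everyone, this is (6π − 6π)/12 = 0. Stable differences between people have already cancelled within each person. So steering can distort the average only through carry-over, or through a drift over time that does not cancel between the two orders.

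**The case against.** Much of the case on the other side stands.

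- **A reader might infer that allocation ceases to be random, or that the trial is not truly randomized.** The article does not support that. Fair lots with a cap of six are a form of restricted randomization, in which each participant's chance of either order, before any lot is drawn, is 1/2. Every fixed 6 + 6 scheme has a determined tail, including the list recommended below (1.71 of 12). The fault is that the tail is visible to the screener.
- **A reader might take 23% as the size of the problem.** That holds only for independent lots. With a 6 + 6 set the stated rule adds nothing to the tail of any balanced list; with independent lots it adds 2.71 − 1.71 = 1.0 participant per group.
- **A reader might infer a biased treatment effect, or damage to a first-period or carry-over analysis.** The Data analysis section describes no such analysis. It compares readings before and after needling, each session has its own baseline, the cap guarantees equal sequence sizes, and a wash-out is planned.
- **A reader might infer that entry was steered.** Nothing shows this. Most patient entry criteria are numerical or factual, consent comes first, and the researchers who process and analyse the data are blinded.

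These points limit the harm. None of them hides the count from researcher one, and the examination-based criteria still leave some discretion.

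**Conclusion.** The point holds as a concealment weakness of moderate to minor weight. One researcher both decides eligibility and draws the lots, and an expected 1.7 to 2.7 of 12 order allocations per group (14% to 23%) are predictable to that person. This rests on three assumptions: the switch occurs when one order reaches six, lots A and B are equally likely, and the method of drawing is one of the two cases shown.

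The consequence is confined to who receives which order and when. It biases the treatment contrast only if carry-over or a drift over time exists. The documents give no basis for sizing such a bias, so none is claimed. The sample size is not affected.

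**What to change.** 1. Delete the order-of-arrival sentence, and with it the unclear trigger.
2. Before enrolment, generate for each group a random list of six traditional-first and six sham-first, placed in sequentially numbered, sealed, opaque envelopes.
3. Have the envelopes prepared and held by an existing team member who does not screen. Researcher three is a natural choice: that person must learn the treatment anyway and has no stated screening role, whereas researchers four and five are to stay blinded.
4. Open the next envelope only after eligibility and consent are recorded and the first session's pre-needling measurements are done.
5. Keep allocations and running counts from researcher one. Most of the gain comes from this step, because the end of a 6 + 6 list is predictable to anyone who keeps the count.

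The cost is a little preparation with existing staff; the sample size, procedures and analysis do not change. Because recruitment has begun, participants already allocated keep their order and the list covers only the remaining places. The benefit there is partial, since researcher one already knows the counts so far. The report should state how many participants in each group were allocated by order of arrival.
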